#### Data Analysis

To assess the app’s effectiveness, differences between the app and no-app groups will be examined with respect to homework completion. We will also explore group differences in treatment outcomes. Although randomization will be used to mitigate group differences, potential differences between groups will be examined. If differences are found on variables that may be related to homework completion or treatment outcome (symptom severity/diagnosis, age, sex distribution, history of psychotherapy and pharmacological interventions, comorbid mental health problems, therapist), these variables will be included as covariates in the analyses. Descriptive analyses will be performed on demographic characteristics, comfort with computers, and retention rates (participants assessed at posttreatment and follow-ups). To avoid bias in parameter estimates, missing data will be handled by performing intent-to-treat analyses, in which missing values are replaced using the last observation carried forward, a method appropriate for randomized designs [114].

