#### Study Design

We will conduct a multisite, randomized controlled pragmatic clinical trial in routine clinical settings to test the app’s effectiveness under real-world conditions in order to enhance external validity and ensure successful implementation without sacrificing scientific rigor. A pragmatic clinical trial also suits the nature of mHealth technologies, which require ongoing improvement and are subject to rapid technological change [95-97]. After pretreatment assessment, participants will be randomly assigned to receive a manualized CBT treatment either with app support (app group) or without it (no-app group). Youth assigned to CBT with the app will receive CBT treatment for 12 weeks with the app included (app group). They and their therapists will be shown how to use the app. Youth assigned to receive CBT treatment for 12 weeks with paper-based homework will be in an active control condition (no-app group). Both groups will be in treatment for 12 weeks, the typical duration of CBT. However, therapists in both the app and no-app groups will be able to provide additional sessions should they deem it clinically relevant. Duration of CBT will be recorded and group differences will be analyzed. Following the pretreatment assessment and exclusions, participants providing informed consent will be randomly assigned to treatment group. Random assignment will be done at each test site separately by the site coordinator. At each site, half the participants will be assigned to each group in order to control for site-specific variables (eg, type of CBT delivered, professional background of therapist). To assess the app’s effectiveness both immediately and over time, assessments will be done at the end of the 12-week treatment (posttreatment) and again after 6 months (follow-up 1) and 12 months (follow-up 2). At each time-point, participants will receive a CAD$30 gift card as an honorarium.

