#### Sample Size and Power

Given the low rates of homework completion in research to date, we expect that the app will have at least a moderate effect on homework completion compared with the no-app group [28,35,36]. A power calculation, based on a comparison between 2 groups (app vs no-app) across 4 occasions (pre, post, follow-up 1, follow-up 2) for a single measure, indicates that a sample size of 35 for each group would provide power of 0.84 to detect a moderate effect size for homework completion at α = .05. To allow for dropouts [98], we will recruit 100 youth between 12 and 18 years of age (10 per group at each site). As noted earlier, treatment dropout rates can be substantial and adherence to homework is often quite low. This has been taken into account in calculating the sample size. The expectation is that compliance will be greater for the app than the no-app group. Based on previous research with youth [98], we expect a 10% rate of attrition at each of the 2 follow-ups.

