##### Homework Completion

Effects of the app on homework completion will be analyzed separately for homework quantity and quality. Psychometric properties of the measures will be examined and correlations will be computed to examine congruence between adolescent and therapist sources of information. If warranted, aggregate scores will be computed; otherwise, separate analyses will be done using different measures. To test the hypothesis that the quantity and quality of homework will be greater in the app compared with the no-app group, we will test group differences in quantity and quality scores. We will also explore timing effects, given evidence suggesting that homework completion varies over time and may decrease over the course of treatment [36]. Scores for the first 4, middle 4, and final 3 weeks of homework will be averaged, creating 3 assessment points, and a mixed-model repeated measures multivariate analysis of the variance will be performed with the between factor of group (app vs no-app), the within factor of time (early, middle, late), and the 2-way interaction of group × time.

Exploratory analyses will also be performed. Subgroup analyses will explore differences in the app’s impact on homework completion as a function of test site and gender. Correlations will explore relations between cognitive profiles and homework completion. For the app group, psychiatric and cognitive assessment data will be aggregated and advanced analytics will be performed to examine predictive relations between patient attributes (anxiety, depression, cognitive profile) and the quantity and quality of homework completion. These analyses will include homework completion data logged by the app (proportion of the task completed, the time spent on the task, and the number of visits to the assignment page).

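### The main homework comparison adjusts for covariates only if a baseline difference is seen, and its model omits site, the factor within which the trial randomises

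*Protocol article*

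**What the plan says.** Study Design (Phase 3): "Random assignment will be done at each test site separately by the site coordinator". The reason for equal allocation within site is given: "At each site, half the participants will be assigned to each group in order to control for site-specific variables". Sample Size and Power sets the target: "we will recruit 100 youth between 12 and 18 years of age (10 per group at each site").

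Data Analysis (Phase 3): the groups will be examined for differences. "If differences are found on variables that may be related to homework completion or treatment outcome", then "these variables will be included as covariates in the analyses". Six items are listed: severity or diagnosis, age, sex, past psychotherapy and drug treatment, comorbidity, and therapist. Site is not among them, and nothing says how large a difference must be to count.

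Homework Completion: the model has "the between factor of group (app vs no-app), the within factor of time (early, middle, late") and their interaction. It has no site term and no covariate that is always present. Site appears in this section only in exploratory subgroup analyses.

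Treatment Outcomes: the continuous measures are analysed by group and time, always with the pretreatment value as a covariate. Site again appears only in subgroup analyses.

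**The concern.** Under sound randomisation, an observed baseline difference in a patient characteristic is a chance event. What decides whether adjustment helps is how well a variable predicts the outcome, not whether the arms happen to differ on it. A rule triggered by imbalance admits a weak predictor that is out of balance by luck and leaves out a strong one that is level. With no criterion stated, it also leaves the content of the main model to judgement after the data are in.

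Site is the clearest case. The Implementation Plan says the sites were chosen to vary in location, setting, specialisation and staffing, so differences between them are to be expected. Equal allocation within site removes site differences from the comparison of the arms. A model without site still counts those differences as error, so the reported standard error exceeds the real one. Homework is rated during treatment and has no pretreatment value, so the homework model contains nothing that would absorb such variation.

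**Working it through.** **The plan's own power figure.** Sample Size and Power says "a sample size of 35 for each group would provide power of 0.84 to detect a moderate effect size for homework completion", "based on a comparison between 2 groups (app vs no-app) across 4 occasions (pre, post, follow-up 1, follow-up 2) for a single measure". Moderate is taken as f = 0.25 (assumed). For the between-group F test with N = 70 and m = 4 occasions, the noncentrality is N·f²·m / (1 + (m − 1)ρ), where the within-person correlation ρ is not given.
- ρ = 0.30: 70 × 0.0625 × 4 / 1.90 = 9.21, power 0.849
- ρ = 0.32: 17.5 / 1.96 = 8.93, power 0.838
- ρ = 0.35: 17.5 / 2.05 = 8.54, power 0.821
- ρ = 0.50: 17.5 / 2.50 = 7.00, power 0.742

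So 0.84 is matched for ρ of about 0.30 to 0.35. The calculation has no site or covariate term and cannot settle the present point.

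**Chance entry of covariates.** The plan gives no threshold. If a difference meant p<.05 and the tests were independent, the chance that at least one of k variables enters by luck is 1 − 0.95^k.
- k = 6 (items as listed): 1 − 0.735 = 0.265, or 26%
- k = 7: 0.302
- k = 9 (compound items split): 0.370, or 37%

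**Leaving site out.** Let s be the share of outcome variance due to site. The plan gives no value, so 0.05 to 0.10 is assumed. With equal allocation within site, the real variance of the group difference contains only 1 − s. The unadjusted test uses nearly the whole variance.
- Upper limit for SE inflation, 1/√(1 − s): 1.026 at s = 0.05 and 1.054 at s = 0.10.
- With five sites and 50 per arm, the expected within-arm sample variance is (1 − s) + s × 40/49. The SE ratio is √(0.9908/0.95) = 1.021 at s = 0.05 and √(0.9816/0.90) = 1.044 at s = 0.10. Simulation of 20,000 trials gave 1.02 and 1.05.
- Actual two-sided alpha by normal approximation, 2[1 − Φ(1.96/√(1 − s))]: 0.044 and 0.039. The same simulation gave 0.046 and 0.040.
- Power lost by omitting site alone (single endpoint, d = 0.5, 35 per arm, normal approximation): 0.574 − 0.554 = 2 points at s = 0.05 and 0.597 − 0.555 = 4 points at s = 0.10. At s = 0 both are 0.552, so nothing is lost.

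**Leaving out prognostic covariates.** Simulation, 4,000 runs per setting: one covariate, s = 0.10, d = 0.5, single endpoint, 35 per arm. The correlation r of covariate with outcome is assumed, and the trigger is taken as p<.05. The first three columns give the true spread of the estimate.

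| r | no adjustment | adjusted if different | fixed covariate | power, adjusted if different | power, fixed covariate plus site |
|---|---|---|---|---|---|
| 0.3 | 0.228 | 0.227 | 0.220 | 0.57 | 0.63 |
| 0.5 | 0.227 | 0.220 | 0.195 | 0.56 | 0.72 |

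The conditional rule recovers little of the precision that a fixed covariate gives: 0.220/0.227 is a 3% smaller spread at r = 0.3, and 0.195/0.220 an 11% smaller one at r = 0.5. At 50 per arm, power moves from 0.72 to 0.79 (r = 0.3) and from 0.72 to 0.86 (r = 0.5). Adding site to a fixed covariate leaves the true spread almost unchanged and corrects the reported standard error.

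**The case against.** The strongest reply is that this is a modest efficiency point in a condensed article. Much of it stands.

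- A reader might infer that no covariate is ever fixed. That is not so: Treatment Outcomes always includes the pretreatment value for continuous symptom measures and treats maladaptive cognitions and quality of life the same way. The point is confined to homework, which has no such baseline, and to the missing site term.
- A reader might infer that omitting site throws away the control that stratified allocation provides. It does not. Equal allocation within site prevents confounding by site whatever model is fitted. Only the standard error suffers, and it errs on the safe side. Additive site differences also cancel from the group × time contrast, so only the group main effect is touched.
- A reader might infer that site is ignored altogether. It appears in exploratory subgroup analyses, and therapist, which is on the list, would carry some site information if it entered. Neither adjusts the overall comparison as planned.
- The plan speaks of examining differences, not of testing at .05, and limits candidates to variables thought to be related to outcome. The 26% and 37% are therefore illustrations. A therapist difference also need not be chance, since the article does not say that therapists are randomised.

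The argument that a fuller analysis plan may supply the site term carries less weight. The article does not merely stay silent: it states a conditional rule and lists the factors of the model.

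**Conclusion.** The concern holds for the main homework comparison. As written, the covariates depend on the observed data with no criterion, and the randomisation factor is outside the model and could not enter through a trigger based on imbalance. No bias and no inflated false-positive rate follow from leaving site out.

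The cost is lost precision and a main model that is not settled in advance. For site alone, with an assumed variance share of 0.05 to 0.10, it amounts to a standard error about 2% to 5% too wide, an actual alpha of about 0.046 to 0.039 and 2 to 4 points of power at 35 per arm. The covariate part depends on correlations that the article does not give: small at 0.3, appreciable at 0.5, and near zero if the variables are not prognostic. The change is worth making because it is cheap and uses variables already collected.

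**What to change.** - Delete the baseline-difference trigger and present baseline characteristics by arm descriptively.
- Include site as a fixed effect in the homework model and in the models for the continuous treatment outcomes.
- Name in advance a short list of prognostic covariates for the homework model, for example pretreatment severity, age and sex, to be included whatever the observed balance.
- Keep the pretreatment value already specified for the continuous treatment outcomes.

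Cost: five sites use 4 degrees of freedom. Two severity scores (MASC-2 and CDI-2), age and sex would use 4 more, so about 8 out of 100 participants, with no new data. A random effect for therapist is not needed to repair this point, and the chi-square tests on diagnosis and the t-test on satisfaction can stay as they are.

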### Support for Practice and Learning

Reflecting homework’s critical importance for the success of treatment, there is a direct association between homework completion and outcomes of CBT for anxiety or depression across a wide age range [28,31-34]. However, rates of homework completion are uniformly low across the age spectrum. Studies of adolescents in CBT for depression show that completion rates hover at approximately 50%, are highly variable, and tend to decline across sessions [28,35,36]. These findings may be partly attributable to insufficient support for practice and learning during the interval in between therapy sessions. Although the guidelines for administering homework are intended to ensure that practice occurs, much depends on the patient’s ability to continue practicing without the support that was provided during the treatment session. Whereas in-session learning occurs with the help of a therapist who provides encouragement, feedback, and problem-solving support, learning outside the session is a self-directed effort. The absence of the therapist’s support during the intervals between sessions may jeopardize the conduct of homework assignments.

Consistent with this interpretation, adolescents’ reflections on CBT homework suggest that they experience insufficient support for doing homework. In a CBT program for depression [37], adolescents regarded homework as important, but reported not always completing the assigned exercises because they did not feel motivated or found it too time-consuming. In another CBT program for depression, which consisted of a computerized program designed as a self-help computer game [38], adolescents gave various reasons for not completing homework, including lack of interest and not having a helpful resource. These findings suggest that homework as traditionally administered provides insufficient support for learning. Rates of homework completion may improve if greater support were provided. Adolescents especially are likely to benefit from enhanced support. Adolescence is a period of ongoing cognitive development involving growing understanding of abstract concepts relevant to CBT, and thus a time when support for learning is likely to be particularly important [39].

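### Last observation carried forward is fixed as the missing-data rule to avoid bias, but with the declining homework and dropout the protocol itself describes, it can cause bias

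*Protocol article*

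**What the plan says.** The Phase 3 Data Analysis section gives one rule for missing data, ahead of the homework and treatment-outcome subsections and so governing both: "missing values are replaced using the last observation carried forward, a method appropriate for randomized designs". The same sentence presents this as part of an intention-to-treat approach and names protection of the estimates against bias as its purpose.

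Three other places bear on whether that rule suits this trial:

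- Support for Practice and Learning, on earlier studies of adolescents in CBT for depression: "completion rates hover at approximately 50%, are highly variable, and tend to decline across sessions".
- Homework Completion, introducing the early, middle and late analysis, cites evidence that "homework completion varies over time and may decrease over the course of treatment".
- Sample Size and Power: "treatment dropout rates can be substantial and adherence to homework is often quite low". The same section expects better compliance in the app group. Its only attrition figure is for after treatment: "we expect a 10% rate of attrition at each of the 2 follow-ups".

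**The concern.** Carrying the last value forward assumes that a youth who leaves would have stayed at the last recorded level. The protocol describes homework as something that may fall over treatment and plans an analysis of that fall. A score frozen in week 3 and copied into weeks 9 to 11 is then too high.

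The two reasons offered do not repair this. Randomisation makes the arms comparable at entry. It does not make outcomes flat after dropout, nor dropout alike in the two arms. Intention-to-treat says who is analysed and in which arm. It does not say how gaps are filled.

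At stake are the late-period homework contrast, the group-by-time test and the description of the time trend. The overall homework contrast is affected less. The exploratory symptom outcomes are affected if youth are lost before posttreatment, because the pretreatment value is then the one carried forward.

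**Working it through.** The protocol gives no figure for the effect of carry-forward, so there is none to reproduce. Nor does it give a slope, a standard deviation or an in-treatment dropout rate. The sizes below rest on assumptions and show a range; they do not predict this trial.

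**Inputs from the protocol:** weekly homework scores in blocks of 4, 4 and 3 weeks (11 weeks); completion of about 50% with a tendency to decline; recruitment of 50 per group.

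**Assumptions:** completion falls in a straight line from 60% to 40%, that is 2 points a week, averaging 50%. Everyone gives a first score. A constant weekly dropout hazard, unrelated to the scores, reaches a total p by the last week.

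**Formula.** Number the weeks t = 0 to 10. The weekly hazard is h = 1 - (1 - p)^(1/10). The amount by which carry-forward lifts the mean at week t is

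S(t) = 2 × Σ (k = 0 to t-1) (1 - h)^k × h × (t - k).

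For p = 0.30, h = 0.0350. In the last three weeks S is 2.33, 2.88 and 3.48, with mean 2.89.

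| Dropout by last week | Lift, early block | Lift, late block | Lift, all 11 weeks |
|---|---|---|---|
| 10% | 0.05 | 0.92 | 0.410 |
| 15% | 0.08 | 1.40 | 0.622 |
| 20% | 0.11 | 1.89 | 0.840 |
| 30% | 0.17 | 2.89 | 1.297 |
| 40% | 0.24 | 3.96 | 1.786 |

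The lift is proportional to the slope: half as large at 1 point a week, twice as large at 4.

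**No true effect, same decline in both arms (app minus no-app):**

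- Dropout 15% app, 30% no-app: late 1.40 - 2.89 = -1.5; all weeks 0.622 - 1.297 = -0.7.
- Dropout 20% app, 40% no-app: late 1.89 - 3.96 = -2.1; all weeks 0.840 - 1.786 = -0.9.
- Dropout 40% app, 20% no-app: the sign reverses, to about +2.1 in the late block.
- Dropout 30% in both arms: the group difference is 0. The early block truly averages 57 and the late block 42, a change of -15. Carry-forward shows -15 + (2.89 - 0.17) = -12.3.

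**App halts the decline at 60%, dropout 30% in both arms:**

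- Late difference: true 60 - 42 = 18; carry-forward 60 - (42 + 2.89) = 15.1.
- Group-by-time (late minus early): true 15; carry-forward 15 - 2.72 = 12.3.
- All weeks: true 60 - 50 = 10; carry-forward 10 - 1.30 = 8.7.

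**Simulation** (50 per arm; assumed between- and within-person SD 18, random-slope SD 1):

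- No effect, 20% app and 40% no-app: type I error was about 6% for the all-weeks contrast, 7-8% for the late block and 9-10% for group by time. A likelihood analysis of the same data gave a late difference of -0.1.
- App halts the decline, 30% in both arms: the late difference averaged about 15 with 91-92% coverage of the nominal 95% interval, and coverage for group by time was 87-88%. The likelihood analysis gave a late difference of 17.9.
- App halts the decline, 10% in both arms: the late difference was 17.0 against a true 18, with coverage of 94%.

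**Symptoms.** If the pretreatment score is carried forward, the false difference equals the difference in dropout times the mean improvement. An assumed 20% versus 10% loss before posttreatment and a 1-SD improvement give 0.10 × 1 = 0.10 SD.

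**The case against.** The strongest case on the other side is about size and certainty. Much of it stands.

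- **Main contrast.** The hypothesis concerns the group difference in homework scores; timing is explored in addition. In the no-effect examples the all-weeks bias is 0.7 to 0.9 points, roughly 0.04 to 0.05 SD on the assumed SDs, and it runs against the app. This stands.
- **Bias is not automatic.** With equal decline and equal dropout the group contrast is unbiased. At 10% dropout in both arms coverage hardly moves. In a simulation where dropout was missing at random rather than completely at random (20% and 39%, no effect), the false late difference was only -0.3. This stands.
- **Differential dropout.** A reader might infer that the protocol expects more dropout without the app. It expects better compliance with the app, which may only restate the adherence hypothesis, and it gives no dropout rate by arm.
- **False symptom benefit.** A reader might infer that carry-forward would manufacture one. The stated attrition falls after posttreatment, where the posttreatment score would usually be carried. The 0.10 SD example needs unequal earlier loss, which the documents do not state, and these outcomes are exploratory.
- **Understated uncertainty.** A reader might also object that filled-in values make standard errors too small. In the simulations carry-forward's late-block standard error matched its own sampling SD and was only 2-6% below the sampling SD of the likelihood analysis. This is not a main ground.
- **The alternative also assumes something.** A missing-at-random model estimates homework as if the youth had stayed, which cannot be verified. This is a reason to state the assumption and test it, not to keep carry-forward.

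None of this rescues the statement that carry-forward avoids bias because the design is randomised.

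**Conclusion.** Wrong as written, and it should be fixed. The fault is a stated rule with a false justification, not a detail left to an analysis plan.

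If homework declines and youth drop out for reasons unrelated to their scores, carry-forward overstates late homework and flattens the time trend. Whether the group contrast is biased, and in which direction, depends on whether decline or dropout differs between arms. The documents settle neither. On the assumed 2 points a week with no true effect, unequal dropout costs about 1.5 to 2.1 points in the late period and 0.7 to 0.9 over all weeks. If the app halts the decline, 30% dropout in both arms removes about 3 of 18 points from the late difference, so a real effect of the kind the trial hopes for is understated.

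It would go too far to conclude that the main homework result would be overturned. The documents give no slope or dropout rate that would support that.

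**What to change.** In the Phase 3 Data Analysis section:

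1. Delete the statement that last observation carried forward avoids bias and suits randomised designs. Keep intention-to-treat as the rule that every randomised youth is analysed in the assigned arm.
2. Make the main homework analysis a likelihood-based mixed model for repeated measures, fitted to all observed weekly or period scores.
3. Use the same kind of model for symptom scores at posttreatment and both follow-ups, with the pretreatment value as covariate.
4. State the missing-at-random assumption and add one sensitivity analysis that departs from it, for example homework set to zero after a youth leaves treatment, or a delta shift for symptom scores.

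The cost is a change of wording, slightly more programming and an assumption that must be stated openly. No new data are needed. The change should be made before outcome data are analysed by group.
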